##### Perceived enjoyment of exercise

2.6.3.5

We will measure survivors' perceived enjoyment of physical activity using the Physical Activity Enjoyment Scale (PACES) [36] at T0, T2, and T4. The 16-item scale is scored on a 5-point Likert scale, with higher scores indicating higher level of enjoyment. The PACES has been validated to use in the assessment of children and older adolescents aged up to 18 years [37] and has been commonly used among paediatric oncology populations [38].

##### Health-related quality of life

2.6.3.6

Health-related quality of life (HRQoL) will be assessed using the EQ-5D-Y-5L [39] at T0, T2, and T4. The EQ-5D-Y-5L has previously been used to assess HRQoL in children diagnosed with cancer [27] and has a good test-retest reliability of 0.84 [40]. The questionnaire comprises five dimensions; ‘mobility’, ‘looking after yourself’, ‘doing usual activities’, ‘pain or discomfort’, and ‘feeling worried, sad or unhappy’, answered on a 5-point Likert scale ranging from (1) ‘no problems’ to (5) ‘extreme problems/cannot’. The EuroQOL Group’s visual analogue scale accompanies the EQ-5D-Y-5L where participants self-report their health on a scale from 0 to 100 (0 ​= ​worst health you can imagine, 100 ​= ​best health you can imagine).

##### Aerobic fitness

2.6.3.7

We will assess aerobic fitness remotely using the 6-Minute Walk Test (6MWT) during telehealth sessions at T0, T2, and T4. The 6MWT has commonly been used to assess aerobic fitness in childhood cancer survivors [41] and has been validated to be conducted remotely [42]. We have previously assessed aerobic fitness remotely using the 6MWT in a home-setting, administered by parents of survivors [27]. Prior to conducting the fitness assessment, the AEP will screen participants using a short safety screening questionnaire adapted from Bowman et al. [43] (Supplementary Material S1). After passing the safety screening questionnaire, survivors will wear their activity tracker and collect a resting heart rate (after being seated for at least 1 ​min). To complete the 6MWT, survivors will be encouraged to walk as fast as possible (without running) within 6 ​min around a 30 ​m track. We will provide equipment (30 ​m-long rope and cones) for survivors to distinguish the track. Survivors will be instructed to walk around the rope, completing as many laps as possible. A parent or adult will be present to provide verbal encouragement, record the number of laps completed, and record the survivor’s heart rate at each minute. Immediately after the test, the supervising AEP will ask survivors to rate their perceived intensity of the test using the Borg Rating of Perceived Exertion scale (0 ​= ​rest, 10 ​= ​maximal effort) [44] and record their heart rate. The supervising AEP will record each participants' 6MWT distance results and calculate their aerobic fitness percentile level using normative data [45]. We will manually enter their aerobic fitness percentile into our REDCap database.

##### Muscular strength

2.6.3.8

We will use the five-repetition sit-to-stand test to assess survivors' muscular strength remotely at T0, T2, and T4. The sit-to-stand is a test of strength and endurance relevant to motor skills related to daily activities of living. The five-repetition sit-to-stand test has shown to be a reliable and valid test to measure functional muscular strength in children with cerebral palsy [46], and has commonly been used in paediatric oncology settings [47]. The survivor will be asked to sit up from a chair to a standing position five times with crossed arms as quickly as possible. The test will be timed by their supervising parent or adult, or by the AEP during the telehealth consult. Survivors will be encouraged to use the same chair for each assessment.

### Factors that affect implementation to inform scale-up

2.7

To explore barriers and facilitators to the implementation and scale-up of Making Moves, we will conduct a process evaluation guided by the implementation framework: the updated Consolidated Framework for Implementation Research (CFIR) [48]. The CFIR aims to predict or explain barriers and facilitators to implementation effectiveness across a range of innovations and settings. We will conduct CFIR-guided semi-structured interviews with potential future implementors/deliverers throughout T0-T3 including healthcare professionals within hospitals or private clinics (e.g., nurses, oncologists, exercise physiologists) or community organisations. The updated CFIR contains 48 constructs and 19 subconstructs arranged over 5 domains (innovation, outer setting, inner setting, individuals, and implementation process) and is a common framework used in healthcare settings to discern future implementation strategies [48]. We will also conduct CFIR-guided semi-structured interviews with survivors and their parents at T2 to explore their barriers and facilitators to using Making Moves to promote survivors' physical activity self-efficacy.

### Implementation success of Making Moves

2.8

To judge the implementation success of Making Moves, we will collect implementation outcomes including feasibility, acceptability, and cost. We will conduct semi-structured interviews with research staff (e.g., AEP) to seek feedback regarding the implementation potential in their setting, adaptation needs for better fit in their context, and potential implementation strategies needed to support uptake. We will also record implementation data throughout the intervention period and at T2. This implementation data will include healthcare professional time, resources used, and any costs to implementation for survivors and parents.

#### Feasibility

2.8.1

Feasibility according to implementation outcomes defined by Proctor et al., is the extent to which a new treatment or innovation can be successfully used or carried out within a given setting [49]. We will assess feasibility as a potential explanation of the success of Making Moves, reflected in ≥70 ​% recruitment rate, ≥70 ​% retention rate, ≥70 ​% participation rates (number of modules completed and AEP telehealth sessions attended) and no adverse events (defined as an unfavourable or unintended sign, symptom, or diseases associated with study participation). We will grade each adverse event using the National Cancer Institute’s Common Terminology Criteria for Adverse Events [50]. We will assess adverse events via an email message prompt with a link to a REDCap questionnaire to survivors aged 18+ years and to parents of survivors who are <18 years of age. Text messages will be sent to survivors/parents every two weeks during the intervention (i.e., at weeks 2, 4, 6 and 8).

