### Sample size

2.9

A sample of at least 53 participants will provide greater than 80 ​% power to detect a difference in the mean physical activity self-efficacy score after participating in the Making Moves program. We define a meaningful change in physical activity self-efficacy as one that is a standardised increase of 0.4, informed by previous studies assessing physical activity self-efficacy in adolescents [52,53]. With 53 participants, if the within-individual correlation in the outcome between baseline and post-intervention is 0.5 or greater, a paired t-test would have at least 80 ​% power to detect a meaningful difference in mean scores between time-points, using a two-sided significance level of 5 ​%. To allow for 30 ​% attrition from pre-to post-intervention (based on our pilot), we aim to initially recruit at least 76 participants for the baseline assessment.

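### The zero-adverse-event marker of feasibility ignores severity and is likely to be missed at modest rates of minor participation-related events

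*Protocol article*

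**What the plan says.** Section 2.8 (Implementation success of Making Moves) gives the purpose: "To judge the implementation success of Making Moves, we will collect implementation outcomes including feasibility, acceptability, and cost". Section 2.8.1 (Feasibility) then says "We will assess feasibility as a potential explanation of the success of Making Moves, reflected in" four markers. Three are rates of at least 70%, for recruitment, retention and participation. The fourth, joined to them by 'and', is "no adverse events (defined as an unfavourable or unintended sign, symptom, or diseases associated with study participation").

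The same section adds "We will grade each adverse event using the National Cancer Institute’s Common Terminology Criteria for Adverse Events". On ascertainment it says "Text messages will be sent to survivors/parents every two weeks during the intervention (i.e., at weeks 2, 4, 6 and 8"), with the adverse-event questionnaire going to adult survivors or to the parents of minors.

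Section 2.9 (Sample size) fixes the scale: "we aim to initially recruit at least 76 participants for the baseline assessment", so that 53 remain for analysis after 30% attrition. The article states no expected adverse-event rate.

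**The concern.** Three of the four markers tolerate a shortfall of up to 30%; the fourth tolerates none. The definition reaches down to any sign or symptom linked to participation, in a home exercise programme whose videos include high-intensity intervals and explosive strength work (section 2.5, Table 2). A brief, mild, related symptom in one participant misses the marker, and so does one serious related event. The grade that would tell them apart is collected but plays no part in the marker.

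The marker is also a count of zero rather than a proportion. For a fixed risk per person, it becomes harder to meet as more people are enrolled or as events are captured more completely.

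What is at stake is the feasibility conclusion, which section 2.8 uses in judging implementation success. If the marker is missed because of trivial events, the investigators must either report a shortfall that says little about safety or reinterpret the marker after seeing the data.

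**Working it through.** **Inputs from the article.** Recruited: at least 76. For analysis: at least 53. Attrition: 30%. Standardised change: 0.4. Within-person correlation: 0.5. Test: paired t, two-sided 5% (all section 2.9). Prompts: four per participant (section 2.8.1).

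**Step 1: reproduce the plan's own figures.** The standardised mean difference of the paired changes is 0.4/√(2 × (1 − 0.5)) = 0.4. The noncentral t distribution with n = 53 gives power of 81.5%, which agrees with the stated power above 80%. Inflating for attrition, 53/0.70 = 75.7, which rounds up to 76. Both numbers reproduce, so N = 76 and N = 53 are sound to carry forward.

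**Step 2: chance of missing the marker.** Let p be the probability that a participant has at least one participation-associated event of any grade. The article gives no value, so p is an assumption shown over a range. With participants independent,

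P(miss) = 1 − (1 − p)^N.

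| Assumed p | P(miss), N = 76 | P(miss), N = 53 |
|---|---|---|
| 0.1% | 7.3% | 5.2% |
| 0.5% | 31.7% | 23.3% |
| 1% | 53.4% | 41.3% |
| 2% | 78.5% | 65.7% |
| 3% | 90.1% | 80.1% |
| 5% | 98.0% | 93.4% |
| 10% | 99.97% | 99.6% |

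For example, at p = 1% and N = 76, 0.99^76 = 0.466, so P(miss) = 0.534.

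**Step 3: the same relation inverted, N = 76.** The risk at which the chance of zero events equals q is p = 1 − q^(1/76).

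- q = 0.90 gives p = 0.14%.
- q = 0.50 gives p = 0.91%.
- q = 0.10 gives p = 3.0%.
- q = 0.05 gives p = 3.9%.

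**Step 4: the same question per prompt.** There are 76 × 4 = 304 prompts. If prompts are treated as independent, a 0.1% chance of a reportable event at each leaves 0.999^304 = 73.8% for zero events, and a 1% chance leaves 0.99^304 = 4.7%.

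**Step 5: what meeting the marker would show.** For zero events in N, the exact one-sided 95% upper limit is 1 − 0.05^(1/N). That is 3.9% for N = 76 and 5.5% for N = 53. A clean result is therefore still compatible with a true risk of several per cent.

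**The case against.** A reader might infer that the programme is almost certain to be declared infeasible however safe it is. The article does not support that, for three reasons.

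- **The rate matters.** The chance of a miss runs from about 7% at p = 0.1% to 98% at p = 5% with 76 participants. Near-certainty needs an assumed risk of about 4% or more, which the article does not give.
- **Only associated events count.** The definition is already limited to events linked to participation. Medical approval (section 2.4), videos approved by an exercise physiologist (section 2.3), easier and harder options within each video (section 2.5) and safety screening before the walk test (section 2.6.3.7) may all lower p.
- **No verdict rule is written.** Feasibility is described as a possible explanation of success. Nothing says that one missed marker makes the programme infeasible, and the next phase described in the Discussion is not made conditional on it. The 'and' permits a joint pass/fail reading but does not state one.

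It can also be said that graded events will let readers separate trivial from serious harm, and that using 76 overstates the exposure when 30% may leave. Nor is there evidence that the rule would lead to under-reporting: the prompts are fixed in advance.

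These arguments limit the consequence and lower the severity. They do not repair the marker. Related exercise symptoms are exactly what the definition captures. Reporting by grade does not change a marker that ignores grade, and with 53 participants the chance of a miss is still 66% at 2% and 80% at 3%. Nor is this a detail left to a fuller document, because the article itself states the threshold.

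**Conclusion.** The point stands at moderate severity. As written, the marker gives a mild related symptom and a serious related event the same weight, leaves the collected grades unused, and tightens as enrolment grows. Those features need no assumed rate.

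The likelihood of a miss does need one. With 76 participants it is about even at a per-person risk of 0.9%, 90% at 3% and 98% at 5%; with 53 it is 80% at 3% and 93% at 5%. This assumes independent participants, a common risk, and that all 76 (or 53) are fully observed. If exactly 76 are recruited and 53 complete, partial follow-up of those who leave puts the answer between the two columns.

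The supportable conclusion is that the marker is likely to be missed at modest rates of minor related events, and that a miss would not by itself show whether the harm was trivial or serious. The primary outcome, the sample size and the effectiveness analysis are unaffected.

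**What to change.** Before results are known, restate the fourth marker in section 2.8.1 in terms of the CTCAE grade or the seriousness of participation-associated events, at a level the sponsor chooses. The limit to associated events is already in the definition and can stay.

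Separately, report the proportion of participants with any associated event, overall and by grade, with an exact 95% confidence interval, as a descriptive safety outcome rather than a threshold. It would also help to state whether missing a single marker is meant to count against feasibility as a whole.

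The cost is a sentence or two of text and no new CTCAE data, since every event is already to be graded. The downside is that a mild event would no longer count against feasibility; it would remain visible in the descriptive report. Making the change after a miss would look post hoc, so the timing matters.

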#### Acceptability

2.8.2

Acceptability is defined as the perception among implementation stakeholders that a given innovation is agreeable, palatable, or satisfactory [49]. We will assess the acceptability of Making Moves from survivors (including the intervention, digital aspect, educational modules, and AEP services) at T2. We will use an adapted version of the Youth Satisfaction Questionnaire [51] and use open-ended questions regarding participants’ most enjoyed and least enjoyed features of the program and any suggestions for improvement. We will also use a 2-item benefit and burden questionnaire reported on a 5-point Likert scale (0 ​= ​not at all, 4 ​= ​very much), “Was participation in this study beneficial to you in any way?” and “Was participation in this study burdensome for you in any way?”. To assess the acceptability of the module content, survivors will rate their satisfaction at the end of each module using a 5-point star scale (1 star ​= ​very dissatisfied, 5 stars ​= ​very satisfied).

#### Cost

2.8.3

Cost is defined as the cost impact of an implementation effort [49]. We will identify resources relating to the intervention and value any costs associated in delivering Making Moves, collect costs related to the operation, delivery, and uptake of Making Moves, and collect costs related to the intervention incurred for survivors and parents. To evaluate costs incurred to survivors, parents will complete a study-specific questionnaire at post-intervention. The study coordinator and AEP involved in delivering the intervention will also keep detailed notes throughout the intervention on the intervention costs, and any barriers and facilitators to the delivery of the program, and potential improvements or strategies that may be important for future implementors.

### Sample size

2.9

A sample of at least 53 participants will provide greater than 80 ​% power to detect a difference in the mean physical activity self-efficacy score after participating in the Making Moves program. We define a meaningful change in physical activity self-efficacy as one that is a standardised increase of 0.4, informed by previous studies assessing physical activity self-efficacy in adolescents [52,53]. With 53 participants, if the within-individual correlation in the outcome between baseline and post-intervention is 0.5 or greater, a paired t-test would have at least 80 ​% power to detect a meaningful difference in mean scores between time-points, using a two-sided significance level of 5 ​%. To allow for 30 ​% attrition from pre-to post-intervention (based on our pilot), we aim to initially recruit at least 76 participants for the baseline assessment.

### Analysis

2.10

To examine the potential effectiveness of the intervention on the primary outcome (physical activity self-efficacy), we will calculate the change in self-efficacy scores from T0 to T2 (primary endpoint) and from T0 to T4 using mixed effects regression models, with random intercepts per individual, and fixed effects for the time points. We will perform similar analyses for secondary outcomes, modified to suit the outcome measure. To report on participant characteristics, we will use descriptive statistics as appropriate. Semi-structured interviews will be recorded and transcribed using Microsoft Teams, and verified for accuracy. We will analyse interview data deductively and thematically according to the CFIR determinants (intervention characteristics, outer setting, inner setting, process, and characteristics of individuals) and the TDF domains (e.g., knowledge, skills, beliefs about capabilities, beliefs about consequences, motivation, and goals etc.).

### Ethics and dissemination

2.11

This research study is approved by the Sydney Children’s Hospital Network Ethics Committee (2023/ETH01614) and is registered on the Australian New Zealand Clinical Trials Registry (ANZCTR12623000188639). Our team will disseminate information regarding this research study via quarterly newsletters sent to our collaborators and partners (e.g., our Youth Advisory Board, The Kids' Cancer Project). Quarterly newsletters will include study updates on recruitment and preliminary feedback from participants or study staff. Young survivors involved in our Youth Advisory Board have contributed to the conception and development of this intervention and will be involved on an ongoing basis. Our team also plans to submit abstracts to medical and scientific conferences and publish manuscripts in peer-reviewed journals.

## Discussion

3

This study has been designed to assess the potential effectiveness of an online physical activity program, called ‘Making Moves’ on childhood cancer survivors' physical activity self-efficacy. We previously piloted a previous iteration of this distance-delivered program and found that it was feasible to deliver in a home-setting and acceptable among young survivors [54]. We subsequently established a Youth Advisory Board and underwent an iterative process with consumers to improve the program by addressing survivor and parent feedback from the pilot study. Additionally, we conducted multi-perspective focus groups and interviews with survivors, parents, and healthcare professionals to explore their experiences and priorities of using digital health to support healthy behaviours. Findings from these focus groups and collaborations with our Youth Advisory Board led to the co-development of Making Moves. A key strength of our intervention is the person-based co-design approach that we adopted in the development and evaluation cycles when making improvements based on data gained during evaluation phases [55]. Working with consumers in the design, development, decision-making, and evaluation of the intervention is essential to understanding their perspectives and ensuring the intervention is engaging, relevant, and sustainable [56]. Moreover, our multi-perspective approach is highly valuable as it captures differing views based on the experiences of healthcare professionals and parents that are imperative to consider when delivering interventions for young survivors.

This type I hybrid effectiveness-implementation trial also seeks to determine the potential for future adoption, implementation, and sustainability in real-world settings. Digital health interventions are a promising solution to reach and engage young people diagnosed with cancer, including those living in regional and remote areas [57]. Preliminary results have shown that distance-delivered interventions are feasible and acceptable, and may improve health behaviours such as physical activity levels [18,19]. Factors critical for successful integration and implementation within typical clinical settings are also yet to be determined. Our proposed study aims to improve understanding of factors that may affect future adoption and implementation decisions and explore potential avenues for integrating Making Moves into standard practice. Our process evaluation will enable us to identify strategies and barriers related to recruitment, retention, and implementation that we may not otherwise learn if not for this hybrid study design (i.e., conducting an effectiveness trial then subsequently implementation research). In addition, our analysis of the program costs will provide an important insight into the requirements of program delivery and uptake and may assist with considerations for future stakeholders seeking to implement this program. Combining these strategies will allow us to identify what is needed to support implementation in the real world and identify the barriers and facilitators to implementation that will inform our future selection of appropriate implementation strategies. However, a limitation of this trial is its single group design, which means the trial will not compare survivors who participated in the intervention to a usual care group or the intervention without the AEP sessions. This type I trial will be essential for gathering baseline data, priming the study for the next phase where we will conduct comparative analyses using implementation strategies identified from this study.

This study will help to provide evidence on the potential effectiveness of Making Moves in improving childhood cancer survivors’ physical activity self-efficacy, while allowing us to better understand the implementation context in several clinical settings. Our distance-based delivery strategy will bridge the barrier of distance by reaching survivors and families who may struggle to access specialised exercise support in cancer survivorship [58]. Findings from this study will continue to advance understanding of the critical role of exercise in cancer care [1], which is not yet widely implemented within paediatric oncology. Ultimately, our study will help to equip young survivors with the resources to engage in physical activity to improve their self-efficacy, health outcomes, and quality of life after cancer.

